## Methods/Design

### Study design

The FLAME-trial is a multicenter randomized controlled trial. Patients are recruited during the intake consultation at the Department of Radiation Oncology in one of the participating centers. After giving informed consent, patients are randomized either to the standard arm or to the experimental arm. Patients in the standard arm receive radiotherapy according to the current standard [4], namely 77 Gy in 35 fractions of 2.2 Gy to the whole prostate. Patients in the experimental arm receive an additional integrated microboost to the macroscopic tumor to a total dose of 95 Gy in 2.7 Gy fractions.

To ensure unbiased assessment of QoL measurements, the patients are blinded to the actual treatment given (receiving an ablative microboost or not). The treating physician needs to be informed about the actual treatment, to be able to judge the treatment plans. This is unlikely to influence the assessment of the objective primary endpoint of the trial.

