### Secondary endpoints

Secondary endpoints are treatment-related toxicity, QoL and disease-specific survival. Treatment-related toxicity is measured by the Common Toxicity Criteria for adverse events version 3.0 (CTCAE) [43]. The following adverse events are scored: urinary frequency/urgency, urinary retention, bladder spasms, urinary incontinence, genitourinary hemorrhage, dysuria, rectal or perirectal pain, proctitis, diarrhea, flatulence hemorrhoids, anal incontinence, erectile dysfunction. The physician in attendance scores the complaints before treatment, acute toxicity (weekly during treatment and 4 weeks after treatment) and late toxicity (every six months until 10 years after treatment). All symptoms are registered even if they occur only on one single occasion. Grade > 2 is considered severe toxicity.General health-related QoL is measured using the RAND-36 generic health survey [44], cancer-specific QoL using the European Organization for Research and Treatment of Cancer (EORTC) core questionnaire (QLQ-C30) [45], and the prostate tumor-specific QoL using the EORTC prostate cancer module (QLQ-PR25) [46]. The disease- and treatment-related side effects are only a component of health-related quality of life [47]. To address the components of overall well-being, a general instrument is used in addition to the disease-specific questionnaires [48-50]. The RAND-36 assesses physical and social functioning, physical and emotional role restriction, mental health, vitality, pain, general health and change in health. The EORTC QLQ-C30 contains five functional scales, three symptoms scales, a global QoL scale and six single-items. The EORTC QLQ-PR25 assesses urinary, bowel and sexual symptoms and functioning, and the side effects of hormonal treatment. The first questionnaire is handed over to the patient one week before treatment at the Department of Radiation Oncology and the next questionnaires are sent to the patient every six months until 10 years after the completion of the treatment. It is important to measure QoL every 6 months after treatment, to be able to determine the point in time at which the QoL changes, for example due to side-effects after treatment.

For disease-specific survival, death with metastases is considered a death caused by the disease.

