### Safety

An independent data safety monitoring board (DSMB) will evaluate the toxicity and clinical outcome. The DSMB receives an update of the toxicity in total and per treatment arm every 3 months. Serious toxicity, defined as any acute or late toxicity requiring surgical intervention, any grade 4 toxicity, and any not-transient (duration >6 months) late toxicities grade 3, will immediately be reported to the DSMB. An overview of the percentage of biochemical recurrences per treatment arm together with the evaluated number of patients per arm will be sent to the DSMB yearly as well as a statistical comparison of the incidence of serious and less serious toxicities in the two arms. The DSMB decides on stopping or continuing the trial. Exact rules cannot be specified in advance, but an increase in the incidence of toxicity (grade 3-4) with 5% or a smaller, but statistically significant increase, are among the reasons to consider stopping the trial. The DSMB can decide to prematurely stop the trial in case the improvement in the experimental arm is higher than anticipated in the trial design.

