### Data analysis

All analysis will be performed according to the intention-to-treat principle. Cox proportional hazards regression will be used to analyze differences in biochemical failure and disease-specific survival between the two treatment arms. Survival curves will be estimated by the Kaplan-Meier technique. Differences between both groups in the incidence of acute side-effects will be tested with the Chi square test. The incidence of late toxicity will be analyzed actuarially with the Kaplan-Meier method, the log rank test and Cox regression analysis. To analyze differences in QoL between the two treatment groups over the time points, a general linear model repeated-measures analysis of covariance will be performed [52]. A change of 10% (or in general, 0.5 standard deviation) of the scale width is perceptible to patients as a meaningful change [53]. Because of the multiple comparisons for the QoL items, the p-value is set at a conservative 0.01 for determining statistical significance [54]. For all other analyses, which do not include the QoL measures, a p-value of < 0.05 is considered statistically significant.

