A randomized study design is indicated to resolve the problem of confounding effects. To our knowledge, no other randomized controlled trials are being performed to investigate the benefit of an ablative microboost to the macroscopic tumor in prostate cancer patients. Beside Singh *et al*. [20], three other groups performed a pilot study in which a microboost to the dominant tumor region was delivered. Miralbell, *et al*. [16] treated 50 patients, after 64-64.4 Gy in 1.8-2 Gy fractions to the whole prostate, with a hypofractionated boost of 2 fractions of 5 to 8 Gy to the dominant tumor region, delineated by anatomical imaging. After a median follow up time of 63 months, a 5-year biochemical disease-free and disease-specific survival of 98% and 100%, respectively, were reported with acceptable long-term toxicity. Gaudet *et al*. [17] selectively delivered a brachytherapy hyperdosage of ≥ 216 Gy (150% of the prescribed dose) to the macroscopic tumor, defined according to positive areas on sextant biopsy, in 70 patients with localized prostate cancer treated with permanent seed prostate implant. No difference in acute or late toxicities compared to 120 patients with a standard plan were seen. Fonteyne *et al*. and De Meerleer *et al*. [18,19] performed the largest trial in which 230 patients were treated with a mean dose of 81-82 Gy to a dominant lesion, defined by T2 weighted MRI or MRI plus spectroscopy. With the use of IMRT and daily ultra-sound based prostate positioning, the acute toxicity remained low with no grade 3 or 4 acute gastrointestinal toxicity and 7% grade 3 genitourinary toxicity.

Analyses of the actual delivered dose in the first 50 patients included in the FLAME-trial, revealed that it is possible to deliver a high dose to the macroscopic tumor area without compromising the dose constraints for the nearby organs at risk. The influence of the remaining intrafraction and rotational errors using an online position verification protocol is minimal.

In conclusion, the aim of the FLAME-trial is to assess, in patients treated with external beam radiotherapy for prostate cancer, the potential benefit of an additional ablative microboost to the macroscopic tumor on biochemical control. In addition, the subgroup of patients that will develop a local recurrence within the prostate after treatment can be used to obtain accurate dose-effect information for both the dominant lesion and subclinical disease in prostate cancer.

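### Minor: acute toxicity, an ordinal grade, is tested only as an incidence by chi-square; adding an ordinal comparison of worst grade would recover power against a general worsening at almost no cost

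*Protocol article*

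**What the plan says.** Under Secondary endpoints, "Treatment-related toxicity is measured by the Common Toxicity Criteria for adverse events version 3.0 (CTCAE"), scored by the attending physician, with "acute toxicity (weekly during treatment and 4 weeks after treatment") as the acute period. The same section adds "All symptoms are registered even if they occur only on one single occasion" and sets one threshold: "Grade > 2 is considered severe toxicity".

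Data analysis then gives a single method for these data: "Differences between both groups in the incidence of acute side-effects will be tested with the Chi square test". Outside the quality-of-life measures, significance is at 0.05. The article does not say at which grade incidence is counted.

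Two other places bear on which differences matter. Safety lists, among reasons for the monitoring board to consider stopping, "an increase in the incidence of toxicity (grade 3-4) with 5" per cent, and also provides a yearly comparison of both serious and less serious toxicity. The Discussion accepts better local control without a survival gain only if severe toxicity stays limited. It also wants any benefit weighed against drawbacks that include a slight rise in toxicity.

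**The concern.** A chi-square on incidence can be read in two ways. As a two-by-two table at some grade, it treats all grades on the same side of the cut as equal. As a full grade-by-arm table, it uses every grade but not their order, and spends three or four degrees of freedom where a trend needs one. Both discard information already collected.

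The direction of the loss matters because this is a harm comparison. Lower power makes a non-significant result more likely when toxicity has truly shifted upward. The article shows interest in toxicity below the severe threshold (Safety and Discussion, as above), so a shift across grades is relevant to its own aims.

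**Working it through.** **The plan's own figures.** The article states no power, effect size or grade distribution for acute toxicity. Its only power statement, 80% for the primary endpoint, reproduces. The hazard ratio is ln 0.74 / ln 0.64 = 0.675. Schoenfeld's formula needs 4(1.645 + 0.842)² / (ln 0.675)² ≈ 160 events. About 162.6 are expected under the stated accrual, follow-up and loss, giving power of 0.80 to 0.81. This supports the 283 per arm used below and nothing more.

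**Inputs.**
- 283 per arm (abstract), all assumed evaluable.
- 0.05, taken as two-sided. The article does not give the sidedness for toxicity.
- Standard-arm worst grade 3+ of 7%. This is an assumption. The figure comes from a cited boost series in the Discussion, which had "no grade 3 or 4 acute gastrointestinal toxicity and 7% grade 3 genitourinary toxicity".
- Remaining grades assumed, here 20/40/33/7% for grades 0/1/2/3+.
- A general worsening modelled as a common odds ratio (OR), also assumed. An OR of 1.81 takes 7% to 12%: (0.12/0.88)/(0.07/0.93) = 1.81. That is the Safety section's increase read as 5 percentage points.

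**One case by hand, OR 1.5.** The cumulative odds at grades 1+, 2+ and 3+ are multiplied by 1.5: 80% becomes 85.7%, 40% becomes 50%, 7% becomes 10.1%. The experimental mix is 14.3/35.7/39.9/10.1%.

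- Two-by-two at a cut: z = (p₂ − p₁)/√(2p̄(1 − p̄)/283), power ≈ Φ(z − 1.96).
  - Grade 2+: 0.10/0.0418 = 2.39, power 67%.
  - Grade above 2: 0.0314/0.0235 = 1.34, power 27%.
- Unordered table: noncentrality 283 × Σ(p₂ − p₁)²/(p₁ + p₂) = 283 × 0.0242 = 6.84 on 3 degrees of freedom, power about 58%.
- Ordinal (Wilcoxon/proportional odds): V = (566/12)(1 − Σp̄³) = 47.17 × 0.892 = 42.1; z = ln 1.5 × √42.1 = 2.63, power 75%.

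**Simulation, same mix** (20,000 runs; grade 4 split off at 0.1%, which costs the unordered table a little more):

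| Common OR | Ordinal | Grade 2+ (loss) | Unordered table (loss) | Grade above 2 (loss) |
|---|---|---|---|---|
| 1.5 | 74.5% | 65.9% (8.5) | 55.4% (19.1) | 26.7% (47.8) |
| 1.6 | 86.2% | 79.0% (7.2) | 70.5% (15.7) | 35.4% (50.7) |
| 1.8 | 96.9% | 93.3% (3.6) | 88.8% (8.0) | 52.1% (44.8) |

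**Other mixes with 7% at grade 3+, OR 1.5 to 1.8.** The loss is roughly 3 to 14 points at grade 2+ and 5 to 19 for the unordered table. At grade above 2 it is 43 to 49 at the two ends of the OR range, and up to about 52 near OR 1.6.

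**Outside those ranges.**
- With 70/22/7/1% and OR 1.6, the grade 2+ loss is 39 points (77% against 38%).
- With a gastrointestinal-like 40/40/20% and almost no grade 3, at OR 1.5, the losses are 20 points (grade 2+), 17 (unordered) and 69 (above 2).
- With 10/40/43/7% and OR 1.3, the loss at grade above 2 is only 26 points.

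**The reverse case.** Suppose 5 points move from grade 2 to grade 3 and nothing else changes.
- Severe cut: 0.05/√(2 × 0.095 × 0.905/283) = 0.05/0.0247 = 2.03, power 53%.
- Ordinal test: those men move by only (0.33 + 0.07)/2 = 0.20 of the rank scale. The mean shift is 0.05 × 0.20 = 0.010 with standard error 0.0230, so z = 0.43 and power is 7%. Across mixes it is 6 to 9%.

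A shift confined to the grade 2 boundary (40% to 50%) also favours its own cut: 66% against 38%.

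**The case against.** Chi-square on incidence is a valid test; simulated rejection under no difference was 4.7 to 5.8%. It gives a percentage that clinicians read easily. At the severe cut it matches the contrast the article stresses most, grade 3-4 toxicity. For a rise confined to those grades it beats the ordinal test by a wide margin. A uniform worsening is the reviewer's alternative; the article does not specify one. All of this stands, and it is why the point is an efficiency gain in a secondary endpoint and why the severe comparison must stay.

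Four stronger readings are tempting and not supported:

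- That the plan gives up about 50 points of power. This requires incidence to mean grade above 2. The article uses that threshold to define severe toxicity, not to define incidence, and the cut may properly be set in the full protocol or analysis plan. At grade 2+ the loss can be about 3 points.
- That the 7% is a known standard-arm rate. It comes from men who received a boost to the dominant lesion, and the same series had no acute gastrointestinal grade 3 or 4 events.
- That the weekly scoring is wasted. How the scores are reduced to one value may be in the full documents, and a worst-grade analysis does not use the repetition either. The argument rests on grade order alone.
- That adoption hinges on this test. Sample size considerations ties adoption to significantly better efficacy, because toxicity risk is higher. The acceptability condition is in the Discussion and concerns severe toxicity.

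**Conclusion.** The point holds as a minor, inexpensive improvement. Nothing is stated wrongly. The named test ignores grade order, and in every proportional-odds scenario examined it had less power than an ordinal test. The size of the loss is conditional on 283 evaluable men per arm, a two-sided 5% level, 7% at grade 3+ in the standard arm and a common OR of 1.5 to 1.8. On those terms it is modest against a grade 2+ cut, moderate against an unordered table, and large only if nothing below grade 3 is counted. None of those assumptions except the sample size is fixed by the article. The advantage disappears, and reverses sharply, when the harm is confined to grade 3+. Neither analysis alone covers both patterns.

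**What to change.** In Data analysis, extend the acute-toxicity sentence to two parts:

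1. Keep the chi-square comparison of the proportion with any acute toxicity above grade 2, reported with its risk difference, as the severe-toxicity measure.
2. Add an ordinal comparison of each patient's worst acute grade (proportional-odds model or Wilcoxon test), reported as a common odds ratio with 95% confidence interval, separately for genitourinary and gastrointestinal toxicity.

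This needs a sentence or two of analysis wording and no new data. The cost is one more safety test for each organ system, and an odds ratio that is harder to read than a percentage. Keeping the severe-grade percentages beside it answers the second problem.

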### Randomization

Randomization is performed by an independent trial center. If a patient meets the inclusion criteria and has provided informed consent, the physician contacts the trial center. To prevent randomly occurring differences in important prognostic factors across the two randomized groups, the randomization is stratified by TURP, hormonal treatment and by centre. A TURP prior to radiotherapy is associated with significantly more late genitourinary toxicity [23,24]. The likely mechanism of increased late toxicity is related to the relative devascularisation of the urethra after TURP and the decreased capability of the mucosa to repair sublethal damage after radiotherapy [24]. Hormonal treatment is a prognostic unfavorable factor for late genitourinary side effects [23,25] and erectile impotence [26-28]. Furthermore, a protective effect for hormonal treatment is reported for acute gastrointestinal side effects [23,29,30]. To prevent small numbers of patients in a particular hospital from all receiving, by chance, the same treatment, the hospital is chosen as one of the factors for stratified randomization as well.

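### The named toxicity tests make no stated use of the pre-treatment grade or of the TURP and hormone strata, which can dilute an arm difference in toxicity

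*Protocol article*

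**What the plan says.** Under Secondary endpoints, treatment-related toxicity is graded by CTCAE version 3.0 on a fixed list of urinary, bowel and erectile items. On timing: "The physician in attendance scores the complaints before treatment, acute toxicity (weekly during treatment and 4 weeks after treatment) and late toxicity". On recording: "All symptoms are registered even if they occur only on one single occasion". On severity: "Grade > 2 is considered severe toxicity".

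Under Randomization, "the randomization is stratified by TURP, hormonal treatment and by centre". The particular reasons given for the first two factors all concern toxicity. TURP is linked to more late genitourinary toxicity. Of hormones the article says "Hormonal treatment is a prognostic unfavorable factor for late genitourinary side effects", and it adds erectile impotence and a protective effect on acute gastrointestinal effects.

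Under Data analysis, "Differences between both groups in the incidence of acute side-effects will be tested with the Chi square test", and "The incidence of late toxicity will be analyzed actuarially with the Kaplan-Meier method, the log rank test and Cox regression analysis". No baseline grade, covariate or stratum is named for either. The same section plans an analysis of covariance for quality of life.

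**The concern.** The scored items include urinary frequency, incontinence and erectile dysfunction, which a man can have before radiotherapy. Entry excludes an IPSS of 20 or more, so milder urinary complaints are admitted. The first 50 patients had a median age of 70.5 years. A two-arm chi-square has no place for a baseline grade unless the event definition supplies it, and the article gives no rule that an event must be new or worse than at entry.

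If entry complaints are counted, they add events to both arms that the boost cannot have caused. A real excess then looks smaller and is harder to detect. This matters because the Discussion accepts the boost, without a proven survival gain, only if severe toxicity stays limited, and the DSMB receives a yearly statistical comparison of toxicity by arm. TURP and hormonal treatment also explain part of the variation in toxicity, and the named tests leave that information unused.

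**Working it through.** **Plan's own figure.** The article gives no power for toxicity. Its only power statement is for the primary endpoint, and it reproduces. The hazard ratio is ln 0.74 / ln 0.64 = 0.675. With 566 patients and the stated accrual, loss and 3.5 years of further follow-up, one-sided power is 79.7% to 81.5%, depending on the formula and the entry curve. So 283 per arm is a sound basis for what follows.

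**Inputs.** From the article: n = 283 per arm; p < 0.05 for analyses other than quality of life (taken as two-sided); TURP 10/50 = 20% and long-term hormones 26/50 = 52% in the first 50 patients. Assumed, because the article gives no figures: baseline prevalence b, and new-toxicity risks c (standard) and t (boost) among men free of the complaint. Also assumed: entry complaints persist, are scored again and do not depend on arm, and there is no loss to follow-up.

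**Baseline complaints counted.** Each arm shows b + (1 − b) × its new risk, so the difference is (1 − b)(t − c). At b = 10%, c = 10%, t = 18%:

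- Rates: 0.10 + 0.90 × 0.10 = 19.0% and 0.10 + 0.90 × 0.18 = 26.2%; difference 7.2 points instead of 8.0.
- Null standard error: √(2 × 0.226 × 0.774 / 283) = 0.0352. Alternative: √((0.19 × 0.81 + 0.262 × 0.738) / 283) = 0.0350.
- Power: Φ((0.072 − 1.96 × 0.0352) / 0.0350) = about 54%.

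**Only men free at entry.** Here n = 283 × 0.90 = 254.7 per arm, with 10% v 18%. The standard errors are 0.0307 and 0.0305, and power is Φ((0.080 − 1.96 × 0.0307) / 0.0305) = about 74%.

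| New toxicity | b | Rates if counted | Difference (points) | Power if counted | Power, free at entry |
|---|---|---|---|---|---|
| 10% v 18% | 0 | 10.0 v 18.0% | 8.0 | 78.5% | 78.5% |
| 10% v 18% | 10% | 19.0 v 26.2% | 7.2 | 53.5% | 74.1% |
| 10% v 18% | 20% | 28.0 v 34.4% | 6.4 | 37.5% | 69.0% |
| 10% v 18% | 30% | 37.0 v 42.6% | 5.6 | 27.4% | 63.2% |
| 5% v 10% | 5% | 9.75 v 14.5% | 4.75 | 40.9% | 59.6% |
| 5% v 10% | 10% | 14.5 v 19.0% | 4.5 | 29.9% | 57.3% |

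**Check against a worsening rule.** The last column drops men with an entry complaint, whereas a worsening rule keeps them. Suppose all 283 stay in and, at the extreme, no man with an entry complaint worsens. At b = 10% the rates are 0.90 × 10% = 9.0% and 0.90 × 18% = 16.2%. The difference is again 7.2 points, but the null standard error falls to √(2 × 0.126 × 0.874 / 283) = 0.0279 and the alternative to 0.0277. Power is Φ((0.072 − 1.96 × 0.0279) / 0.0277) = about 73%. So most of the loss comes from the added variance of entry complaints, and the worsening rule recovers nearly all of it.

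**Low prevalence, as expected above grade 2.** With 10% v 20%, power if counted against free at entry is 90% v 91% at b = 1% and 88% v 91% at b = 2%. With 3% v 8% it is 67% v 74% and 61% v 73%.

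**Strata alone.** This was simulated with 20,000 runs, no entry complaints, TURP 20%, hormones 52%, control risk 20% in the reference stratum and a treatment odds ratio of 1.8. Plain chi-square against Cochran-Mantel-Haenszel gives 85.7% v 85.7% for stratum odds ratios of 1, 89.6% v 90.4% for 2, and 87.9% v 90.1% for 3. Type I error of the plain test is 4.9%, 4.5% and 3.8%.

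**The case against.** The strongest reply is that the article never says an existing complaint is an event. Registering every symptom is a recording rule, incidence can mean new events, the endpoint is called treatment-related, and scoring complaints before treatment fits an intention to separate old from new. A journal article may also leave the event definition and Cox covariates to a fuller document. This stands against the tempting reading that the plan does count entry complaints: the text leaves that open, so the power loss is conditional.

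Two further replies also stand. Cox regression is planned for late toxicity and could carry the baseline grade and the strata, so one cannot say that every toxicity comparison is unadjusted; the article just names no terms. And randomization balances entry complaints on average, so a reader who infers an invalid test or concealed harm goes too far. Safety review does not rest on these tests alone either: the DSMB gets toxicity by arm every 3 months, serious toxicity is reported at once, and a 5% rise in grade 3-4 toxicity is listed without requiring significance.

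What does not stand is that this is only missing detail. Specific tests are named, the acute one cannot use the baseline grade or strata as it is named, and both are already in hand.

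**Conclusion.** The point holds as a worthwhile improvement to a stated method, not as an error that invalidates it. If entry complaints enter the incidence, the arm difference shrinks by (1 − prevalence). Under 10% v 18% and 283 per arm, power is about 54% rather than 74% at 10% prevalence, a loss of about 21 points.

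That size rests on assumed rates and prevalences, which suit erectile dysfunction and lower-grade urinary items. The 20% TURP and 52% hormone shares are histories and prescriptions, not complaint prevalences, and should not be read as such. Above grade 2, with IPSS of 20 or more excluded, few men should enter with urinary events and the loss is probably small. It is not nil if 1% to 2% do: about 2 to 3 points under 10% v 20%, and 7 to 13 under 3% v 8%. If incidence already means new or worsened events, this loss disappears and the article need only say so. The strata contribute about 0 to 2 points by themselves, and leaving them out makes the test slightly conservative.

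**What to change.** Define a toxicity event, item by item, as a grade above the patient's own pre-treatment grade and at or above the grade analysed, with all randomized men kept in the denominator. Test acute toxicity by Cochran-Mantel-Haenszel over TURP and hormonal treatment (an exact version where counts are small). Test late toxicity by log-rank and Cox stratified by the same two factors. Report arm differences with 95% confidence intervals as well as p-values, and show any-occurrence rates alongside.

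The cost is analysis wording only: the pre-treatment scores and the strata are already recorded. The one small drawback is that worsening-based rates compare less directly with papers that count any occurrence, which the side-by-side display covers.

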**Methods/Design:**

The FLAME-trial (**F**ocal **L**esion **A**blative **M**icroboost in prostat**E **cancer) is a single blind randomized controlled phase III trial. We aim to include 566 patients (283 per treatment arm) with intermediate or high risk adenocarcinoma of the prostate who are scheduled for external beam radiotherapy using fiducial markers for position verification. With this number of patients, the expected increase in five-year freedom from biochemical failure rate of 10% can be detected with a power of 80%. Patients allocated to the standard arm receive a dose of 77 Gy in 35 fractions to the entire prostate and patients in the experimental arm receive 77 Gy to the entire prostate and an additional integrated microboost to the macroscopic tumor of 95 Gy in 35 fractions. The secondary outcome measures include treatment-related toxicity, quality of life and disease-specific survival. Furthermore, by localizing the recurrent tumors within the prostate during follow-up and correlating this with the delivered dose, we can obtain accurate dose-effect information for both the macroscopic tumor and subclinical disease in prostate cancer. The rationale, study design and the first 50 patients included are described.

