### Sample size considerations

The statistical power of the study was calculated for the primary endpoint (five-year freedom from biochemical failure). Based on data of two randomized clinical trials [2,51] reporting the treatment results of patients treated with a radiation dose equal to the dose of the standard arm of our trial, we expect that the five-year freedom from biochemical failure of the standard arm will be approximately 64%. We expect that an additional ablative microboost to the macroscopic tumor will increase this number with at least 10%. A one-sided log rank survival power analysis shows that the length of follow-up after accrual of the last patient should be 3.5 years to detect a difference of 10% (64% and 74% free from biochemical failure after 5 years, in the control arm and experimental arm, respectively) with a power of 80% at a one-sided 5% significance level. This is under the assumption that the patients enter the study during an accrual period of 5 years, 50% of the enrollment is complete when 70% of the accrual time has past and that 20% of the patients in both arms are lost to follow-up during the follow-up period of 5 years. The reason to choose a one sided p-value is that, although extremely improbable, an increase in biochemical failure in the experimental arm would lead to the same action as no difference at all between the two treatment arms. This is because the experimental treatment will only be implemented if it is significantly better than the usual treatment, due to the increased toxicity risk in the experimental arm.

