## Discussion

The FLAME-trial is designed to investigate the effect of an ablative microboost to the macroscopic tumor for patients treated with external beam radiotherapy for prostate cancer.

Previous studies demonstrated that the rate of toxicity after high dose external beam radiotherapy with the use of accurate position verification is low and consequently high QoL is reported [34,63-66]. Planning studies showed that an ablative microboost to the macroscopic tumor was theoretically feasible within the currently used dose constraints for rectum and bladder [15,67,68]. Furthermore, a feasibility study of Singh *et al*. [20] reported excellent early toxicity after simultaneous integrated IMRT boost of 95 Gy to the intraprostatic lesions. As a result, with the use of optimal position verification combined with the currently used dose constraints, the toxicity in the experimental treatment arm with the ablative microboost of 95 Gy is expected to be acceptable.

Previous trials demonstrated a biochemical benefit of dose escalation. However, up to now none of the dose escalation trials were able to detect an improvement in disease specific or overall survival. However, all trials were designed for biochemical survival instead of overall or disease-specific survival due to the natural behavior of prostate cancer. For this reason the FLAME-trial is also powered for biochemical disease free survival. An improvement in local control without a proven benefit in overall survival is only acceptable when severe toxicity remains limited. Furthermore, to establish whether a benefit in biochemical failure free survival also counterbalances the negative aspects of dose escalation, such as a small increase in toxicity, it is important that QoL is taken into account. Therefore, repeated QoL measurements are performed in patients included in this trial.

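### Acceptance of the boost depends on severe toxicity staying limited, but the toxicity analysis fixes only difference tests at p<0.05, and a non-significant result cannot show that condition is met

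*Protocol article*

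**What the plan says.** The Discussion of the protocol article sets a condition on harm: "An improvement in local control without a proven benefit in overall survival is only acceptable when severe toxicity remains limited". It adds that quality of life must be weighed against drawbacks such as a small rise in toxicity. Sample size considerations justifies the one-sided primary test by the higher toxicity risk expected with the boost.

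The analysis of toxicity is in Data analysis. For acute effects: "Differences between both groups in the incidence of acute side-effects will be tested with the Chi square test". For late effects: "The incidence of late toxicity will be analyzed actuarially with the Kaplan-Meier method, the log rank test and Cox regression analysis". Everything outside quality of life is judged at p<0.05, and sidedness for toxicity is not stated. For quality of life the same section names a change that patients would notice; for toxicity it names none. Secondary endpoints defines severe toxicity as CTCAE grade above 2.

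The Safety section does give a size. Among the reasons for the data safety monitoring board (DSMB) to consider stopping is "an increase in the incidence of toxicity (grade 3-4) with 5" per cent, or a smaller but significant rise. It also says that exact rules cannot be fixed in advance.

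The trial is sized for biochemical failure alone: "We aim to include 566 patients (283 per treatment arm", "with a power of 80% at a one-sided 5% significance level".

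**The concern.** The question on harm is whether any excess of severe toxicity is small. A test of no difference asks whether an excess has been demonstrated. When events are uncommon and the sample was chosen for another endpoint, failure to demonstrate an excess says little about how large it might be.

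The final report could therefore present a non-significant toxicity comparison while its data remain compatible with an excess at or above the 5% that the Safety section itself treats as worrying. A reader would have no pre-stated way to tell that result from one that really excludes such an excess. Because the Discussion ties acceptability to this point, it affects how a positive primary result can be used.

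**Working it through.** **1. The plan's own sample size.** Inputs from Sample size considerations: "64% and 74% free from biochemical failure after 5 years, in the control arm and experimental arm, respectively"; one-sided 5%; 80% power; 5-year accrual with half the patients enrolled at 70% of that time; 20% lost over 5 years; and "the length of follow-up after accrual of the last patient should be 3.5 years".

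- Exponential hazards: −ln(0.64)/5 = 0.0893 and −ln(0.74)/5 = 0.0602 per year, so the hazard ratio is 0.675.
- With that entry pattern and loss, the event probabilities are about 0.333 and 0.241. With 283 per arm this gives about 163 events.
- Power by the Schoenfeld formula: Φ(√162.6/2 × 0.3935 − 1.645) = Φ(0.864) = 80.6%.

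The 566 is confirmed for biochemical failure. The article states no power for toxicity.

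**2. Chance of missing a true 5-point rise.** The control-arm rate of severe toxicity is not given, so it is an assumption, shown over 1% to 15%. The 5 points are the Safety section's 5%, read as an absolute difference. The test is taken as two-sided 5%. The lower sample size is 283 × 0.8 ≈ 226 per arm, a crude allowance for the planned loss.

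Power = Φ[(0.05 − 1.96·s0)/s1], with s0 = √(2·p̄(1−p̄)/n) and s1 = √([p1(1−p1) + p2(1−p2)]/n).

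- 5% v 10%, n = 283: s0 = 0.02214, s1 = 0.02204; Φ(0.30) = 0.618; missed 38%.
- 10% v 15%, n = 283: s0 = 0.02780, s1 = 0.02772; Φ(−0.16) = 0.436; missed 56%.

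| Control rate | Boost rate | Missed, 283 per arm | Missed, 226 per arm |
|---|---|---|---|
| 1% | 6% | 10% | 17% |
| 3% | 8% | 26% | 35% |
| 5% | 10% | 38% | 48% |
| 7% | 12% | 47% | 56% |
| 10% | 15% | 56% | 64% |
| 15% | 20% | 65% | 71% |

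Exact binomial enumeration of the uncorrected chi-square test at 283 per arm agrees from a 3% rate upward (24%, 37% and 56% at 3%, 5% and 10%) and gives fewer misses at 1% (6%). If the test were one-sided at 5%, the misses would be 27% and 44% at control rates of 5% and 10%. A two-sided test with 80% power would need 435 per arm for 5% v 10%, and 686 for 10% v 15%.

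**3. What a non-significant result can hide.** Take 14/283 (4.9%) v 25/283 (8.8%), one event short of significance. The difference is 3.9 points with standard error √[(0.0470 + 0.0805)/283] = 0.0212, so the 95% interval is 3.9 ± 4.2, about −0.3 to 8.0 points. An excess well above 5 points is not excluded.

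**4. What an interval could show.** With equal true rates p, the chance that the upper 95% limit falls below 5 points is Φ(0.05/SE − 1.96), SE = √(2p(1−p)/n).

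- n = 283, p = 5%: SE = 0.0183, Φ(0.77) = 78%.
- n = 283, p = 7%: SE = 0.0214, Φ(0.37) = 64%.
- n = 283, p = 10%: SE = 0.0252, Φ(0.02) = 51%.
- n = 226: 68%, 55% and 43%.
- True rates 5% v 7%: SE = 0.0199, Φ(0.03/0.0199 − 1.96) = 32% at 283 per arm, and 27% at 226.

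For late toxicity at five years these are optimistic. Half the patients enter after year 3.5 of accrual, and the analysis falls at 5 + 3.5 = 8.5 years, so only about half have five years of potential follow-up.

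**The case against.** Four points can be made for the plan.

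- **The decision rule.** A reader might infer that a non-significant toxicity comparison would pass as acceptable. The article does not say so. Its only implementation rule is significant superiority on the primary endpoint, and the Discussion describes a judgement that includes quality of life. This stands: the gap is an undefined criterion and not a wrong one.
- **Estimates are planned.** Late toxicity is not merely tested, since Kaplan-Meier curves and Cox regression give incidences and an effect size. This stands too. An article may also leave intervals to the full protocol or analysis plan. But this article does fix the toxicity tests and the significance level, and it ties neither these nor the estimates to the condition in the Discussion.
- **The DSMB.** It sees toxicity per arm every three months, and a 5% rise counts without significance. This is a real safeguard, but a discretionary one during the trial, and it does not govern the final conclusion. Even if an observed rise of at least 5 points also counted as a signal at one look at full data, a true 5-point rise would be missed 37%, 47% and 52% of the time at control rates of 5%, 7% and 10% (283 per arm).
- **A margin would be unfair.** A binding 5-point margin would turn a monitoring trigger into a test the trial was never sized for, and the trial would often fail it with little or no true excess. This stands and limits the fix.

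**Conclusion.** The concern holds as a gap between a stated condition and the analysis meant to inform it. The planned tests at p<0.05 cannot by themselves show that severe toxicity is limited. At assumed control rates of 5% to 10%, a two-sided comparison with 283 per arm leaves a 5-point rise undetected in about 38% to 56% of trials.

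That size rests on three assumptions that the article does not settle: the control rate, a two-sided test, and a comparison of simple proportions standing in for the actuarial late analysis. The figure should not be quoted without the wider range of 10% to 65%.

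Two further readings are not supported. One is that the planned size is enough to rule out a 5-point excess: at equal rates that succeeds 78% of the time at best within the 5% to 10% range. The other is that the plan treats any significant excess as failure; no such rule is written. The point is an inexpensive improvement in reporting and interpretation, and does not touch the primary analysis.

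**What to change.** Add to Data analysis, for grade >2 toxicity, acute and late:

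- The main result is the between-arm difference in incidence (cumulative incidence for late toxicity) with its 95% confidence interval.
- The report states whether that interval excludes the 5-point excess named in the Safety section. The figure is a reference for interpretation and not a binding non-inferiority margin.
- The chi-square and log-rank p-values are kept as description.
- A non-significant p-value is not taken as evidence that toxicity is limited.

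The cost is wording only: grade >2 events are already collected, and no patients or visits are added. The downside is that the trial may have to report that a 5-point excess is not excluded, where it would otherwise have reported no significant difference.
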